### **Data analysis:**

24-hour dietary recalls: The Food Processor software (ESHA Research, Oregon, USA) will be used to analyze the 24-hour diet recalls. Information from the existing regional and local food composition tables, such as the GCC (Gulf Cooperation Council) and Kuwait Food Composition Tables will be used to analyze the UAE traditional composite dishes. Recipe analysis by using the ESHA program will be conducted for UAE traditional composite dishes that contain different ingredients than the Kuwaiti composite dishes.

Statistical Analysis: Data will be analyzed using the Statistical Package for the Social Sciences, version 17.0 for Windows (SPSS, Chicago, U.S.A.). Data will be summarized by means, medians, standard deviations, interquartile range, and percentages as applicable. Differences between the intervention and control group related to the outcomes at 12 months will be tested, with a significance level of 0.05, considering the multilevel structure of the data.

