## **Study Protocol**

### **Study Title: Skills for Change: Development, Implementation and Evaluation of a Community-based Diabetes Nutrition Education Program for Emirati Adults with Type 2 Diabetes**

#### **Project Summary:**

##### **Project Summary:**

The United Arab Emirates (UAE) with a prevalence of 19.5% of diabetes is considered by the International Diabetes Federation as the country with the second highest prevalence of diabetes in the world. Diabetes is a major risk factor for coronary artery disease, a leading cause of death in the United Arab Emirates. Other complications associated with type 2 diabetes are neuropathy and microvascular damage leading to blindness, and end-stage renal disease. Effective diabetes self-management requires that persons with diabetes acquire the necessary knowledge and skills to change their nutrition-related behaviors for optimal metabolic control. Evidence from randomized controlled studies, observational studies, and meta-analyses support the effectiveness of medical nutrition therapy for diabetes management. Despite the high prevalence of diabetes and its complications in the UAE, very few diabetes education intervention studies have been conducted in representative populations in the country.

We propose a one-year, community-based, cluster randomized study involving 400 Emirati adults with type 2 diabetes that will focus on diet and physical activity to decrease sedentary lifestyle and improve food choices and clinical outcomes, including glycemic control and blood lipids. The primary outcome of the intervention is a change in HbA1c. We expect this project driven by theoretical principles of behavior change and education will enhance the diabetes-related knowledge, skills, and behaviors of the participants. The results of this project will serve as an important guide in the development and implementation of culturally adapted future diabetes management nutrition intervention programs for Emirati adults with type 2 diabetes. The study will be conducted in collaboration with Al Ain Ambulatory Healthcare Services, Abu Dhabi Healthcare Services.

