## **Methodology**

### **Design and Participants:**

The seven health centers managed by Al Ain Ambulatory Healthcare Services will be the target setting for this study. The primary end-point for this intervention is HbA1c. We aim at a difference in one-year HbA1c value of one-third of the standard deviation which is approximately 1.8 based on recent data from patients with diabetes attending Ambulatory Health Services clinics in the Emirate of Abu Dhabi. Thus, we expect a 0.6 decrease in HbA1c in the

intervention group. We chose to test this difference with a power of 0.8 and a 2-tailed significance level of 0.05. If randomization had been carried out on an individual basis, we would need  $16 \times 9 = 144$  participants per group. However, we have to take into account group randomization. Assuming a design effect of 2, we need approximately 300 per group. However, there will be a gain in efficiency by adjusting for baseline values. Therefore, 200 participants should be adequate per group (i.e. 200 for intervention and 200 for control). Based on this calculation, the seven health centers were randomly assigned as follows: 3 intervention clinics (Al Yahar, Al Muweiji, & Hilli) and 4 control clinics (Al Maqam, Al Zakher, Niyadat, & Mezyad). The health center setting (urban vs. suburban) and size (large vs. small) were considered during the randomization. The assignment of the health centers to the intervention versus control groups was stratified by the center sizes and center locations. Of the 7 health centers, 3 are large urban centers, two are small urban centers, and two are large suburban centers. One large urban, one large suburban and two small urban centers were randomly assigned to the control group, and the remaining 3 centers were assigned to the intervention group.

Exclusion criteria are: Very advanced age (>70 Y), patients with severe complications, such as renal or heart failure, blindness, or other morbidities that can prevent active participation in the program. Moreover, patients with contraindications to the required physical activity may be excluded from the structured physical activity program upon the recommendation of their attending physicians. Verbal and written informed consent will be obtained from all the participants. Ethics approval for the project will be obtained from the relevant research ethics committees (UAE University Research Affairs and Al Ain Medical District Human Research Ethics Committee).

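### The analysis section does not carry through the baseline adjustment on which the cut from about 300 to 200 per group depends

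*Protocol*

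**What the plan says.** Three places in the protocol bear on the primary analysis.

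- **Project Summary:** "The primary outcome of the intervention is a change in HbA1c".
- **Design and Participants:** the target is a 12-month value: "We aim at a difference in one-year HbA1c value of one-third of the standard deviation which is approximately 1.8". Hence "we expect a 0.6 decrease in HbA1c in the" intervention arm. The test is fixed by "We chose to test this difference with a power of 0.8 and a 2-tailed significance level of 0.05". The section obtains 144 per group for individual randomisation and about 300 after a design effect of 2. It then reduces this to 200 per group on the strength of one sentence, "However, there will be a gain in efficiency by adjusting for baseline values". It gives no correlation, variance reduction or other figure for that gain.
- **Data analysis:** "Differences between the intervention and control group related to the outcomes at 12 months will be tested, with a significance level of 0.05", with a closing clause that the analysis will respect the multilevel structure. No covariate is named.

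Table 1 schedules HbA1c at baseline and at 12 months in both arms, so the data needed for the adjustment will exist.

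**The concern.** The reduction from about 300 to 200 per group is justified only if the primary analysis adjusts for baseline HbA1c. The section that says how the data will be analysed mentions clustering, which is the other half of the sample size argument, but not baseline. Someone who follows that section to the letter would compare 12-month values without adjustment and lose the precision that the sample size already counts on. Someone who starts from the summary might compare raw changes, which has different precision again.

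At stake is the power of the primary comparison at the planned size, and whether the document describes one primary analysis consistently.

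**Working it through.** **Inputs from Design and Participants:** difference 0.6, SD 1.8, two-sided alpha 0.05, power 0.80, design effect 2, 200 per group. **Assumed, because the protocol gives no value:** r, the correlation between baseline and 12-month HbA1c. All power figures use the normal approximation. They take the design effect as unchanged by adjustment and make no allowance for dropout or for the small number of centres.

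**1. The protocol's own chain.**
- Individual randomisation: 2 × (1.960 + 0.842)² × (1.8/0.6)² = 2 × 7.85 × 9, which gives 142 after rounding up. The protocol's 16 × 9 = 144 agrees.
- Design effect: 2 × 144 = 288, which the protocol rounds up to about 300.
- The step to 200 cannot be reproduced, because no correlation is stated. Baseline adjustment multiplies the variance by (1 − r²), so the implied r can be solved for. From 300, 1 − r² = 200/300 and r = 0.58. From 288, 1 − r² = 200/288 and r = 0.55.

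**2. Unadjusted 12-month values at 200 per group.**
- Effective size per group: 200/2 = 100.
- Standard error: 1.8 × √(2/100) = 0.2546.
- Difference over standard error: 0.6/0.2546 = 2.357.
- Power: Φ(2.357 − 1.960) = Φ(0.397) = 65.4%. This does not depend on r.

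**3. The two alternatives over a range of r.** Baseline adjustment multiplies the standard error by √(1 − r²); a raw change score multiplies it by √(2(1 − r)).

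| Assumed r | Power, baseline-adjusted | Power, raw change score |
|---|---|---|
| 0.30 | 69.5% | 51.3% |
| 0.40 | 73.0% | 57.6% |
| 0.50 | 77.7% | 65.4% |
| 0.55 | 80.6% | 70.0% |
| 0.60 | 83.8% | 75.0% |
| 0.65 | 87.3% | 80.4% |
| 0.70 | 91.0% | 86.1% |

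Example at r = 0.5, adjusted: 2.357/√0.75 = 2.722, and Φ(2.722 − 1.960) = 77.7%.

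**4. Reading the table.** With adjustment, 200 per group gives 80% power once r is about 0.55 or more. A raw change score needs about 0.65 or more; at r = 0.5 it does no better than the unadjusted comparison, and below that it does worse. The unadjusted comparison stays at 65% and, on the protocol's own chain, needs 288 to 300 per group.

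**The case against.** The strongest reply is that the passages are compatible. The analysis section is one general sentence covering every outcome. It names no model and does not call the comparison unadjusted. The sample size section shows that adjustment was intended, and Table 1 collects what is needed. Covariates are commonly left to a statistical analysis plan, and one may exist that names baseline HbA1c. This stands as far as it goes: a reader might infer that the protocol prescribes an unadjusted analysis, and the text does not support that. What remains is that the only analysis text picks up one premise of the sample size, clustering, and leaves out the other. That is a gap between two sections of the same document, not just detail left for later.

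A reader might also infer that the protocol sets out three incompatible analyses, of which only the adjusted one can support 200 per group, leaving the choice open until the data are seen. That goes too far. Change is an outcome, not a model, and change analysed with baseline as a covariate gives the same treatment effect as the baseline-adjusted 12-month value. Even a raw change score reaches 80% if r is about 0.65 or more. Whether the choice is really open depends on a plan that is not shown.

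Finally, a reader might size the problem with a test on the 5 degrees of freedom that seven centres leave (7 − 2). At r = 0.577 that gives 48% unadjusted and 64% adjusted. Since the repaired analysis also falls well short, those figures mainly reflect the number of centres. That is a separate issue and should not be used to measure this one.

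**Conclusion.** The point holds as a failure to carry the adjustment through, and it should be fixed. The sample size relies on baseline adjustment, the analysis section does not secure it, and the summary's wording of the primary outcome differs from the 12-month value used for the sample size.

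Taken literally, the analysis sentence costs about 15 percentage points of power: 65% against the planned 80%. That figure rests only on the protocol's difference, SD, design effect and group size, under the normal approximation. The figures for the other two analyses also depend on the assumed r. The values of 0.55 to 0.58 are back-solved from the reduction itself, so they show what the protocol needs to be true, not what is known. The documents do not support a claim that the trial will be analysed without adjustment.

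**What to change.** Make three changes of wording:

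1. In *Data analysis*, state that 12-month HbA1c is compared between arms in the multilevel model with the participant's own baseline HbA1c as a covariate.
2. In the *Project Summary*, describe the primary outcome in the same terms.
3. In *Design and Participants*, state the baseline-to-12-month correlation assumed behind 200 per group, with its source. If it is below about 0.55, the reduction to 200 does not deliver 80% power even with adjustment, and the size needs to be revisited.

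The cost is a few sentences. No extra measurement is needed, since baseline HbA1c is already in Table 1 for both arms.

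### The stated 80% power at two-sided 0.05 makes no allowance for having only seven randomised centres; on 5 degrees of freedom the protocol's own inputs give about 62–64%

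*Protocol*

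**What the plan says.** Under Design and Participants, the protocol sets the operating characteristics for HbA1c: "We chose to test this difference with a power of 0.8 and a 2-tailed significance level of 0.05". The target difference is 0.6, one third of an SD of about 1.8. The size under individual randomisation is given as 16 × 9 = 144 per group. Clustering is then brought in: "Assuming a design effect of 2, we need approximately 300 per group". An unquantified gain from adjusting for baseline brings this down to 200 per group, 400 in all.

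The same section fixes the number of randomised units: "the seven health centers were randomly assigned as follows: 3 intervention clinics" and "4 control clinics". Allocation was stratified by size and location; of the seven centres, "3 are large urban centers, two are small urban centers, and two are large suburban centers".

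Under Data analysis, differences between the groups at 12 months are to be tested at 0.05 in SPSS 17.0, "considering the multilevel structure of the data". No model, reference distribution or degrees-of-freedom method is named. The ICC and the correlation between baseline and 12-month HbA1c are not stated anywhere.

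**The concern.** In a cluster-randomised trial, the arm effect is judged against variation between centres. Seven centres less two arm means leave 5 degrees of freedom to estimate that variation. A design effect inflates the variance, but it does not account for how poorly that variance is estimated from so few centres. The cost appears in the critical value: 2.571 on 5 degrees of freedom against 1.96 on the normal scale.

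The stated level and the stated power therefore pull against each other. If the test holds 0.05, the power falls well short of 0.8. If the power is secured by testing against 1.96, the false-positive rate exceeds 0.05. Readers who rely on the stated 80% would over-interpret a null result, and a test against 1.96 would give intervals that are too narrow.

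**Working it through.** **Inputs.** From Design and Participants: SD 1.8, difference 0.6, two-sided 0.05, power 0.8, design effect 2, 200 per arm, 3 against 4 centres, three size/location strata.

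**1. The protocol's own figure.** The multiplier is 2(1.96 + 0.84)² = 15.7, rounded up to 16. With (1.8/0.6)² = 9, 16 × 9 = 144, as stated. The 16 is a normal-theory constant. Doubling gives 288, which the protocol rounds to about 300.

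**2. What the step to 200 implies.** Baseline adjustment multiplies the variance by 1 − r².
- 300 to 200: 1 − r² = 0.667, so r ≈ 0.58.
- 288 to 200: 1 − r² = 0.694, so r ≈ 0.55.

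**3. Standard error and signal.** SE = 1.8 × √(2 × 2/200 × (1 − r²)).
- r ≈ 0.58: SE = 0.208; 0.6/0.208 gives a noncentrality of 2.89.
- r ≈ 0.55: SE = 0.212; 0.6/0.212 gives 2.83.

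**4. Power on each reference.** The t rows use the non-central t distribution.

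| Reference | Critical value | r ≈ 0.55 | r ≈ 0.58 |
|---|---|---|---|
| Normal | 1.96 | 81% | 82% |
| t, 7 − 2 = 5 df | 2.571 | 62% | 64% |
| t, 7 − 4 = 3 df (two stratum terms added) | 3.182 | 49% | 50% |

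The normal row reproduces the claimed 0.8, so the inputs are read as the protocol used them. The shortfall on 5 df comes from the reference distribution alone.

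**5. Sensitivity to the unstated correlation.** On 5 df, keeping design effect 2:
- r = 0.7: SE = 0.182, noncentrality 3.30, power about 75%.
- r = 0.8: SE = 0.153, noncentrality 3.93, power about 88%.

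**6. False-positive rate of tests that the analysis wording permits.** At 400/7 ≈ 57 per centre, a design effect of 2 implies an ICC of 1/(57.1 − 1) ≈ 0.018. This is an inference, not a stated value. Each scenario used 20,000 simulated trials with no effect, 3 against 4 centres and no stratum terms.

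| Test | Near-equal centre sizes within arm | Unequal centre sizes |
|---|---|---|
| REML mixed model against 1.96 | 8.2% | 8.9% |
| Centre means against 1.96 | 10.5% | 10.5% |
| ML mixed model against 1.96 | 11.5% | 12.0% |
| Uncorrected sandwich against 1.96 | 16.4% | 18.4% |

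An analytic check for centre means: twice the upper tail of t on 5 df beyond 1.96 is 10.7%. Judged against 2.571, the centre-mean t test gives 5.0% with near-equal sizes. A separate simulation of 3,000 trials put a REML model with Satterthwaite degrees of freedom at 5.4%. At an assumed ICC of 0.005, REML against 1.96 gives only about 5.5%.

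**The case against.** The strongest reply is that the analysis section never says the test will use a normal reference. The normal constant belongs to a planning shortcut, and a planning approximation does not bind the analysis. A mixed model with small-sample degrees of freedom or a centre-level t test fits the same words and holds about 5%. The choice between them is the kind of detail a statistical analysis plan settles, and that plan is not at hand. The 16% figure also needs an uncorrected sandwich variance, which the protocol does not mention, and every error rate above depends on an ICC that it does not state.

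All of this stands. A reader might infer that the trial's primary test has a false-positive rate of 8–16%, or that it fails to hold 0.05. The protocol does not support that: it names no reference distribution, and valid tests fit its wording. The error rates show only what the wording would let through.

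The reply does not reach the power statement, which is a figure given in the protocol itself. A later analysis plan can choose a valid test, but that choice cannot make the stated power true at these inputs. A second reply is that baseline HbA1c may be more predictive than the implied 0.55–0.58. That is possible, and r = 0.8 would restore more than 80% on 5 df; but the protocol states no correlation, and the gain it actually takes does not go that far.

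**Conclusion.** The power statement is wrong as written. With seven centres, two-sided 0.05 and power 0.8 do not both hold at the protocol's own inputs: power is about 62–64% on 5 degrees of freedom, some 16–18 points below the stated 80%, and about 49–50% if the strata enter the model.

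This rests on design effect 2, a baseline gain of about one third inferred from the step to 200, and a t reference with degrees of freedom counted from the centres. Power for a REML model with Satterthwaite or Kenward-Roger degrees of freedom was not computed and may differ somewhat.

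On the analysis wording the conclusion is conditional: it permits tests that would run at roughly 8–16% at an ICC near 0.018, and equally permits tests that hold about 5%.

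**What to change.** In Design and Participants, restate the power on a reference with cluster-level degrees of freedom, and give the assumed ICC and baseline correlation. If the size and location strata will be in the model, count them. This does not call for enrolling more participants: extra patients in the same seven centres add no centre-level degrees of freedom.

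In Data analysis, state that the arm effect on 12-month HbA1c is tested in one of two ways:
- a mixed model with baseline HbA1c as covariate, a random intercept for centre, and Satterthwaite or Kenward-Roger degrees of freedom; or
- a baseline-adjusted centre-level t test.

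The change takes a few sentences. Its cost is a less favourable stated power and wider intervals, up to 31% wider on 5 df (2.571/1.96 = 1.31).

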### **Potential Benefits to Participants:**

The study does not provide monetary or other compensation to the participants. However, there are other potential benefits as a result of participation in the intervention, including: (1) Improved nutrition knowledge and skills for diabetes self-management; (2) Healthier food choices; (3) Increased physical activity levels; (4) Improved clinical outcomes (blood glucose, body weight, and blood lipids); (5) Increased self-efficacy for adopting a healthy lifestyle; (6) Improved metabolic control may contribute to the prevention of chronic complications of diabetes.

### **Safety Considerations**

There are no risks associated with participation in the study, except normal potential risks related to blood sample drawing which will be minimized by following standard protocols of the health centers. Blood collection will be performed by certified personnel assigned by the health centers to this task. Inconvenience related to the time spent on completing study questionnaires and attending educational activities will be minimized by arranging suitable times with the participants.

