### **Relevance of the proposed work to the UAE community:**

To our knowledge, this project is the first community-based intervention focusing mainly on diabetes nutrition education in the UAE and thus it can serve as an important guide in the development and implementation of future diabetes management intervention programs in the country. The potential Benefits of the intervention include (1) Improved nutrition knowledge and skills for diabetes care; (2) Healthier food choices and increased physical activity levels; (3) Improved clinical outcomes (blood glucose, body weight, and blood lipids); (4) Culturally-appropriate exercise video to increase the physical activity levels of adults with diabetes and families; (5) Model community-based diabetes nutrition intervention program that has the potential to improve participant nutrition knowledge and skills; (6) Appropriate recommendations for larger scale programs in the UAE that have the potential to improve nutrition knowledge, skills, and clinical outcomes of adults with diabetes; (7) Increased scientific knowledge: Identification of the potential impacts of culturally-adapted diet intervention and regular practice of moderate physical activity on metabolic parameters.

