|     |                                      | 
The concepts of frequency and intensity will be defined by using easy to understand explanations and words.
 
Recommendations on safe practice of physical activity (management of glycemia, shoes and feet...) for people with type 2 diabetes will be provided
 
The session will be an interactive discussion involving the patients on the type, frequency and intensity of activities the patient is used to do at this time
                                                                                                     |
| # 3 | Estimating food portions             | 
Dietitian discusses food portion estimation skills and demonstrates using real foods, food models, and household common measures (cups, spoons, etc.). Includes participant exercises involving estimations of different food portions, including UAE traditional food and composite dishes.
 
Participants "guesstimate" before they actually measure and then compare answers.
 
Food models, samples of real foods, household measuring utensils (cups, spoon, etc.) are used.
 
Consistent carbohydrate intake is emphasized
 |
|     | To be active in the daily life       | 
An interactive discussion will be organized with the patients to identify some easy way to be active in the daily life and tips will be provided by the educator.
 
The role of family and friends as support will be emphasized
                                                                                                                                                                                                                                                                                                           |
| # 4 | Choosing healthy fats                | 
Importance of both type of fat and amounts for good health is discussed; Benefits of using herbs & spices instead of fat are emphasized. Participants share recipes and their ideas for modification. Low fat cooking demonstration is conducted (if facilities are available)
                                                                                                                                                                                                                                                              |

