### **Physical Activity Sessions:**

The participants will be invited to attend six-week exercise group sessions. The exercise classes, including basic resistance, flexibility, and aerobic exercises will be designed in collaboration with an exercise educator. Sessions will be offered separately for men and women by using indoor and/or outdoor exercise facilities. In addition; participants will be advised to perform exercise sessions at home (3 to 4 sessions per week) exercising at a level of 9 on the Perceived Exertion Scale. The amount of physical activity will be increased progressively through the intervention by encouraging the participants to perform longer and more intense sessions. A video describing sessions, of different durations and at different intensities, providing some explanations and recommendations about the practice of physical activity will be given to each of the participants to help them practice of physical activity at home. This video will be produced in collaboration with UAEU Center for Educational Technology (CET). The physical activity program will be based on the theoretical principles of motivation, self-efficacy, goal-setting, and social support as well as on the simple premise that physical activity can be increased throughout the day at work, at home, and during leisure time. The educational component of physical activity will focus on both physical activity and sedentary behavior as described in the section above. Education will be combined with exercise training sessions. Group exercise sessions will be facilitated by a nurse and exercise specialist. The duration of each session will be 60-90 minutes.

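### The safety section admits no risk beyond blood drawing, which contradicts the protocol's own exercise precautions, and no harms item is collected that could compare the arms

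*Protocol*

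**What the plan says.** Safety Considerations is the only section on risk. It states: "There are no risks associated with participation in the study, except normal potential risks related to blood sample drawing". The only other burden it names is the time taken by questionnaires and education.

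Other parts of the Protocol treat exercise differently:

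- **Design and Participants:** "patients with contraindications to the required physical activity may be excluded from the structured physical activity program", on the advice of the attending physician.
- **Table 2, group session 2:** "Recommendations on safe practice of physical activity (management of glycemia, shoes and feet...) for people with type 2 diabetes will be provided".
- **Physical Activity Sessions:** "The exercise classes, including basic resistance, flexibility, and aerobic exercises will be designed in collaboration with an exercise educator". Classes last 60 to 90 minutes. Participants are also advised to exercise at home three to four times a week, "exercising at a level of 9 on the Perceived Exertion Scale". The same section adds: "The amount of physical activity will be increased progressively through the intervention by encouraging the participants to perform longer and more intense sessions".

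The Data collection section lists six categories: dietary intake, nutrition knowledge, physical activity, treatment satisfaction, anthropometry and biochemistry. Table 1 schedules the assessments at baseline and 12 months.

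Informed Consent and Confidentiality summarises the information sheet and ends with a general undertaking that problems during the project will go to the ethics committee and the Ambulatory Healthcare Services.

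**The concern.** An activity that has contraindications, and that needs precautions for glycaemia and feet, is one the authors regard as carrying some risk. The safety section says otherwise, so the document contradicts itself on a matter that the ethics committee and participants rely on.

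The statistical stake is the comparison of harms. Exercise is given to one arm only, so any hypoglycaemia, injury, foot problem or cardiovascular event that it causes would appear as a difference between arms. If harms are not among the data collected, the trial can report benefit but cannot set harm beside it. That matters because the sections on relevance and expected outcomes present the project as a guide for larger programmes.

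**Working it through.** No figure in the plan has to be reproduced. The check sets the passages side by side.

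**1. Is the risk statement compatible with the rest?** Safety Considerations makes one exception, blood drawing. Design and Participants recognises contraindications to the exercise, and speaks of that activity as required. Session 2 of Table 2 plans safety advice specific to people with type 2 diabetes. Physical Activity Sessions describes exercise that increases in length and intensity. Each of the first two presupposes a risk from exercise, and the third describes the exposure. The statements conflict.

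**2. Who is exposed?** The planned size is 200 per group, 400 in total. The classes and home advice are for intervention participants only. Those with contraindications may be left out of the structured programme, so the number exposed is at most 200 and may be lower. The documents do not say by how much.

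**3. Would the planned data show harm?** None of the six listed categories is a harms category. Table 1 alone would be weak evidence, because it also omits nutrition knowledge and total cholesterol, which the text lists. Here, however, list and table agree: neither has an item for adverse events, hypoglycaemia, injury or cardiovascular events. The treatment satisfaction questionnaire is described only as a measure of satisfaction, not as a source of harms data.

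**4. Does another provision fill the gap?** The general undertaking to report problems gives no definition of an event, no form, no timing and no method of asking. The steering committee's remit in Intervention Monitoring and Evaluation covers recruitment, training and implementation difficulties and does not name safety. Neither would give counts that can be compared by arm.

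**5. Does the safe-practice advice stand in for disclosure?** It comes in a group session, after enrolment. Participants are encouraged to attend at least three of five sessions. Without session 2, 5 − 1 = 4 remain, and 4 ≥ 3, so a participant can meet that target and never receive the advice.

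**6. What does the consent section show?** Its summary of the information sheet has four items: aim, data collection methods, right to refuse a question, and right to withdraw. None is a risk item. For intervention centres it gives individual and group education as examples of what will be explained and does not mention exercise. This describes the summary only.

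**The case against.** The strongest reply is that the protocol does handle risk in practice. It excludes people with severe complications such as renal or heart failure, lets physicians recommend exclusion from the exercise programme, has a nurse and an exercise specialist run the classes, and undertakes to report problems. Participants are invited, advised and encouraged rather than made to exercise. All of this stands and limits the likely harm. It does not remove the contradiction, since each safeguard confirms that a risk was foreseen. Nor does it give harms data by arm.

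Some stronger readings are tempting but not supported:

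- **That participants would consent on a wrong risk statement.** The information sheet is not at hand, and the examples in the consent section are not presented as exhaustive. Only the Protocol's summary can be judged.
- **That harms would go unrecorded.** The general reporting route means some could be recorded. What is missing is systematic collection.
- **That Table 1 lacks a safety item because risk was denied.** The documents give no reason for the omission.
- **That every intervention participant would do the exercise.** The exclusion for contraindications rules this out.
- **That the home exertion level contradicts the stated moderate intensity.** The phrase "regular practice of moderate physical activity on metabolic parameters" stands in a list of expected benefits, not in an exercise instruction. The range of the exertion scale is not given, so the documents do not show whether level 9 is high or low.

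**Conclusion.** The point holds as a contradiction in the text and a gap in the data plan. The Protocol foresees exercise-related risk in two places and denies it in its safety section. The component concerned is given to one arm of up to 200 participants, and no listed item would allow harms to be compared with the 200 planned controls.

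This should be corrected before the trial starts, but it does not threaten the primary HbA1c comparison. The conclusion rests on the Protocol text alone. It assumes nothing about how often harms occur and makes no claim about the content of the information sheet.

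A secondary point is that the home exercise level is given as a number on a scale whose range is not stated, so the instruction cannot be interpreted from the document. No view is taken on the exercise level or on who should exercise.

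**What to change.** 1. Reconcile Safety Considerations with Design and Participants, session 2 of Table 2 and Physical Activity Sessions, and check that the participant information agrees with the result.
2. Add a short harms item to the Data collection list and to Table 1, covering hypoglycaemia, injury or foot problem, cardiovascular event and hospital attendance. Ask it in identical words in both arms at the existing 12-month assessment and report it by arm.
3. Have the clinical team state which exertion scale is meant and its range.

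**Cost.** An ethics amendment, and a few minutes for each of about 400 participants at a visit already planned. No new visit or procedure is needed.

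**Limits.** Recall of minor events over 12 months will be incomplete. Ascertainment may also differ by arm. Intervention participants have 7 dietitian visits and up to 5 group sessions, so up to 7 + 5 = 12 scheduled contacts before exercise classes are counted; no such contacts are described for controls. Asking the same questions of both arms at the same visit reduces this difference but does not remove it, and the report should say so.
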